## Methods/design

### Study design

In primary teeth, vital pulp therapy goals are the pulp tissue regeneration and the maintenance of the physiological process of deciduous tooth exfoliation. Despite its biocompatibility, MTA has a longer setting time, difficult handling, high cost, and potential for tooth discoloration. Thus, this study aims to evaluate clinically and radiographically the pulp repair after the use of a new dentin-pulp biostimulation chitosan membrane in primary teeth with deep occlusal and occlusoproximal cavities reaching more than 3/4 of the total thickness of carious dentin evaluated by periapical radiograph, with at least two thirds of root length. This will be a double-blinded parallel-group randomized controlled trial composed of two groups: group 1 (G1—control), teeth treated with mineral trioxide aggregate (MTA), and group 2 (G2—experimental), teeth treated with the new dentin-pulp biostimulation chitosan membrane.

Before study group assignment, the allocation concealment will be performed to trial participants in sequentially numbered, sealed envelopes. This closed envelope will include a randomization number. Allocation concealment will be ensured, as the team responsible will not release the randomization number until the patient has been recruited into the trial. The operator will open the envelope and will find the treatment condition to be conducted in the patient. The operator then gives the information about treatment allocation to the patient. The team responsible for recruitment is not allowed to receive information about the group allocation.

One primary tooth per patient will be randomly allocated in each group. If the patient has more than one tooth to include in the study, the tooth closest to the inclusion criteria will be chosen. The allocation criteria will be the cavity type (occlusal and occlusoproximal) and the child’s age. Group allocation will be randomized through computerized stratified sampling (Microsoft Excel®), independently, that is, the patients and legal guardians will remain blinded to intervention group status. Randomization will occur close to the moment of the intervention [18]. Blinding the operator during the allocation sequence and application step will not be possible. The intervention group identifier will be assigned at random and will not be identified during data analysis, that is, the examiners will remain blinded.

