### Interventions

#### Clinical procedures

All clinical procedures of this study will be performed by one previously trained and calibrated operator (post-graduate student). A detailed anamnesis and clinical examination will be performed. Next, an intraoral clinical examination with the aid of dental mirror and air jet will screen eligible molars. Then, a periapical radiograph of the eligible primary molars will be taken to verify the furcal conditions. Satisfying all inclusion criteria of the study and after informed consent is given, treatment will be randomly provided in the second visit, according to previously described allocation. The patient and legal guardians will remain blinded regarding the treatment type [32].

After tooth prophylaxis with rubber cup and prophylactic paste (Herjos Tutti Frutt, Vigodent, São Paulo, Brazil), washing, and drying, local anesthesia will be applied (articaine 4% + epinephrine 1:100.000) [28–31]. The cavity preparation will be performed under rubber dam isolation, using water-cooled diamond burs, and caries will be completely removed from the lateral walls and enamel-dentine junction with the aid of low speed round burs (KG Sorensen®, São Paulo, Brazil). The pulp chamber roof will be removed with the aid of round diamond burs (1014-1015) at high speed under copious irrigation. The coronal pulp will be removed with the aid of hand excavators. Pulp vitality will be checked by cut resistance, red color, and hemostasis after 5 min. If necessary, constant irrigation will be performed with sterile saline solution. Pulp stumps will be dried with sterile cotton pellets, and the capping material will be applied according the assigned group [28–31]:

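### The protocol does not clearly keep the unblinded operator out of screening, and its rule for choosing among several eligible teeth is a judgement that can also choose the randomization stratum

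*Protocol article*

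**What the plan says.** All of this is in the protocol article, under Study design and Clinical procedures.

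- **Choice of tooth** (Study design): "If the patient has more than one tooth to include in the study, the tooth closest to the inclusion criteria will be chosen". No measure of closeness, tie-break or decision-maker is given.
- **Stratification** (Study design): "The allocation criteria will be the cavity type (occlusal and occlusoproximal) and the child’s age". The method is given as "Group allocation will be randomized through computerized stratified sampling (Microsoft Excel®), independently". Blocks, block size and a separate envelope series per stratum are not mentioned.
- **Separation of roles** (Study design): "The team responsible for recruitment is not allowed to receive information about the group allocation".
- **Who sees allocations** (Study design): "The operator will open the envelope and will find the treatment condition to be conducted in the patient", and "Blinding the operator during the allocation sequence and application step will not be possible".
- **How many operators** (Clinical procedures): "All clinical procedures of this study will be performed by one previously trained and calibrated operator (post-graduate student").
- **Screening** (Clinical procedures, two sentences later): "Next, an intraoral clinical examination with the aid of dental mirror and air jet will screen eligible molars". The person who does this is not named.

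The envelopes are sealed and sequentially numbered, and the randomization number is withheld until the child has been recruited. Treatment is allocated at the second visit, after screening and consent.

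**The concern.** Sealed envelopes hide the next assignment. They do not hide past assignments from the person who opened them. If that person also judges eligibility or picks the study tooth, the separation promised under Study design is lost at the step where it matters.

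The tooth rule adds a specific route. Age is the same for all of a child's teeth, but cavity type belongs to the tooth. In a child with one eligible tooth of each cavity type, the choice of tooth decides which stratum the child enters. Someone who knows the allocation history and expects a particular arm next in one stratum could, knowingly or not, match easier or harder teeth to an arm. That would be selection bias arising before the envelope is opened.

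**Working it through.** **1. Can the rule rank eligible teeth?** The inclusion and exclusion criteria under Eligibility (tooth type, restorability, lesion depth beyond a threshold, minimum root length, absence of pathology) are each met or not met. Two teeth that meet all of them are equally close. The rule gives no order, so judgement decides.

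**2. Who knows the earlier allocations?** One operator performs all clinical procedures and opens the envelopes. That person has seen every earlier allocation.

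**3. Does that person screen?** The screening examination and the radiograph of eligible molars sit under Clinical procedures, just after the one-operator sentence. The natural reading is that the operator performs them, but the sentences are passive. One eligibility criterion does fall within the operator's procedure: hemostasis within 5 minutes, which Eligibility says is checked at the time of the clinical procedure. Set beside the bar on the recruitment team, the sections leave it unclear whether the operator is outside the eligibility decision.

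**4. How far could the choice of tooth steer allocation?** The article has no figure to reproduce. The following is an illustration under assumptions that the article does not state: 1:1 permuted blocks, a separate series for each cavity type, a chooser who knows all earlier allocations, and the envelope opened as soon as the tooth is chosen.

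Let f be the share of the wanted arm among the assignments left in a stratum's current block. The chooser takes the tooth whose stratum has the larger f, so the chance of the wanted arm is E[max(f1, f2)].

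*Blocks of 2.* Half the time a stratum is at the start of a block (f = 1/2). Half the time one assignment is left, and it is equally likely to be wanted (f = 1) or not (f = 0). So f is 0, 1/2 or 1 with probability 1/4, 1/2, 1/4. For two independent strata:
- P(max = 1) = 1 − (3/4)² = 7/16
- P(max = 1/2) = (3/4)² − (1/4)² = 8/16
- P(max = 0) = 1/16
- E[max] = 7/16 + 4/16 = 11/16 = 68.8%

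*Blocks of 4.* f is 0, 1/3, 1/2, 2/3 or 1 with probability 1/6, 1/8, 5/12, 1/8, 1/6. The same step gives E[max] = 127/192 = 66.1%.

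A simulation of 40,000 children, each with one eligible tooth in each stratum, agrees with the exact values to within simulation error:

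| Randomization within stratum | Wanted arm, simulated | Wanted arm, exact | Next assignment certain to be the wanted arm, simulated |
|---|---|---|---|
| Blocks of 2 | 68.9% | 68.8% | 44% |
| Blocks of 4 | 66.1% | 66.1% | 31% |
| Blocks of 6 | 64.5% | 64.4% | 24% |
| Blocks of 8 | 63.5% | 63.1% | 19% |
| Unblocked | n/a | 50% | 0% |

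In the unblocked case each assignment is an independent 1:1 draw. Changing the tooth changes the envelope but cannot target an arm.

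**5. Whom does this affect?** Only children whose eligible teeth differ in cavity type. The article does not give their share, so no trial-wide bias can be computed.

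**The case against.** The strongest reply is that the article never says the operator screens molars or chooses the tooth. Recruitment takes place at schools and treatment at the university clinic, and a separate recruitment team is mentioned. Follow-up examinations belong to two other examiners, so the heading Clinical procedures need not make every examination the operator's. This stands. A reader might infer that the operator is the screener and that the stated separation has failed. The text supports only that the sections are in tension and must be reconciled.

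The safeguards also count. The number is released only after recruitment, and allocation waits for the second visit. If the tooth is fixed at screening, other children may draw from the same stratum in between, which weakens prediction. But the article does not say that the tooth is fixed at screening.

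Four stronger readings should be set aside:

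- **That the rule admits a tooth that only nearly qualifies.** The sentence applies to a child with several teeth to include, so each candidate is naturally read as already qualifying. The rule is a vague tie-break.
- **That the judgement goes unrecorded and so cannot be examined later.** The article describes no such record, but a condensed article's silence does not show that none exists.
- **That the next arm can be guessed 75%, 71% or 68% of the time with blocks of 2, 4 or 6.** The arithmetic is right: [n + (2^(2n)/C(2n,n) − 1)/2]/(2n) for blocks of size 2n. It measures correct guesses in a single series, not the chance of reaching a wanted arm by choice of tooth, and it also assumes blocks.
- **That missing block details are a fault.** An article may leave these to the full protocol.

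**Conclusion.** The point holds in a limited form. Two parts rest on the text alone: the tooth rule cannot do what it is meant to do, and Study design and Clinical procedures leave unclear whether the one person who knows all earlier allocations is kept out of screening and tooth selection. Because cavity type is a stratification factor, the undefined choice can also set the stratum.

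The size of any bias is conditional. It requires a chooser who knows the allocation history, permuted blocks with a separate series per stratum, and a child with eligible teeth of both cavity types. Given all three, and an envelope opened at the time of choice, the chance of the wanted arm rises from 50% to about 69%, 66% and 65% for blocks of 2, 4 and 6. With unblocked randomization it remains 50%. The document does not show that steering has happened or would happen. The change is worth making because the gap is easy to close.

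**What to change.** 1. State that eligibility and the study tooth are decided by someone without knowledge of earlier allocations, such as the recruitment team or one of the blinded examiners, and reconcile Study design with Clinical procedures accordingly. State also how the hemostasis criterion, which is judged during the procedure, fits with this separation.
2. Replace the closeness rule: every candidate tooth must meet all criteria, and if more than one does, the study tooth is picked at random or by a fixed order set in advance (for example, lowest tooth number).
3. Record the chosen tooth and its stratum on a dated form before the envelope is released. The team that already withholds the randomization number can release it against that form.
4. If blocks are used, keep their details from the operator.

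The cost is a few sentences of protocol text, one form and some examiner or recruiter time at screening. The staff are already in the trial. Trial status says that recruitment was not complete, so the change could apply to the remaining children.

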### Study setting

Participants will be recruited at municipal schools of Bauru, Sao Paulo, Brazil. The children and legal guardians will be instructed about the research and will read and sign a free and clarified consent term. The treatments will take place in the Pediatric Dentistry Clinics of University of Sao Paulo (Bauru, Sao Paulo, Brazil). Efforts will be made to achieve adherence by explaining the treatment importance. This study will consider the patient-centered, public health, and economic outcomes. Recruitment will take place from December 2019 to August 2020. Each participant will be enrolled in the study for approximately 25 months (1 month for treatment plus 24 months of follow-up), and vital pulp therapy procedures will be performed on week 2 to week 12. This clinical trial follows the guidelines for randomized clinical trials (SPIRIT checklist (Additional file 1)).

### Eligibility: inclusion and exclusion criteria

Inclusion criteria will comprise children aged from 5 to 9 years, from both genders, with one restorable maxillary/mandibular first/second primary molar with deep occlusal and occlusoproximal cavities reaching more than 3/4 of the total thickness of carious dentin evaluated by periapical radiograph, with at least two thirds of root length. Exclusion criteria comprised no history of spontaneous pain, internal/external root resorption, fistula/abscess, and lesion at furcal area, and any sign of mobility [1, 2, 28–31]. Also, by the time of clinical procedure, hemostasis will be checked and must occur within 5 min after coronal pulp exposure [28–31]. Exclusion criteria will be the presence of systemic diseases, history of allergic reaction to dental materials, and lack of hemostasis 5 min after coronal pulp exposure (Fig. 1).

**Fig. 1 Fig1:**
[figure not shown]
Flowchart of the study

### Interventions

#### Clinical procedures

All clinical procedures of this study will be performed by one previously trained and calibrated operator (post-graduate student). A detailed anamnesis and clinical examination will be performed. Next, an intraoral clinical examination with the aid of dental mirror and air jet will screen eligible molars. Then, a periapical radiograph of the eligible primary molars will be taken to verify the furcal conditions. Satisfying all inclusion criteria of the study and after informed consent is given, treatment will be randomly provided in the second visit, according to previously described allocation. The patient and legal guardians will remain blinded regarding the treatment type [32].

After tooth prophylaxis with rubber cup and prophylactic paste (Herjos Tutti Frutt, Vigodent, São Paulo, Brazil), washing, and drying, local anesthesia will be applied (articaine 4% + epinephrine 1:100.000) [28–31]. The cavity preparation will be performed under rubber dam isolation, using water-cooled diamond burs, and caries will be completely removed from the lateral walls and enamel-dentine junction with the aid of low speed round burs (KG Sorensen®, São Paulo, Brazil). The pulp chamber roof will be removed with the aid of round diamond burs (1014-1015) at high speed under copious irrigation. The coronal pulp will be removed with the aid of hand excavators. Pulp vitality will be checked by cut resistance, red color, and hemostasis after 5 min. If necessary, constant irrigation will be performed with sterile saline solution. Pulp stumps will be dried with sterile cotton pellets, and the capping material will be applied according the assigned group [28–31]:
Control group—MTA (Angelus®, Londrina, Paraná, Brazil) will be mixed on sterile glass plate according to the manufacturer’s instruction (1 powder spoon to 1 drop of distilled water) for 30 s and placed onto the pulp stumps with the aid of spatula and sterile cotton pellet moistened with distilled water. A thin layer of the material will be assured, based on previous studies [14, 30, 31, 33, 34].BBio group—the dentin-pulp biostimulation chitosan membranes will be previously prepared in the laboratory with equal parts containing 1.5 g of chitosan (Sigma Aldrich, St. Louis, USA), 1.5 g of alginate, and 1.5 g portland cement-based. Each layer will be individually placed and dried at 30 °C for 15 min. Then, the membrane (composed of three layers) will be dried for more 24 h [25, 26]. After preparation and sterilization, the membrane will be placed on the pulp stumps.

For both groups, a thin layer of liner material (Cimpat white – Septodont, Pomerode, Santa Catarina, Brazil) will be placed onto the study materials, inside the pulp chamber. The final restorations will be performed with resin-modified glass ionomer cement (Vitremer® 3M/ESPE) [28–31]. Just after vital pulp therapy, a periapical radiograph will be taken (immediate postoperative radiograph) [28–30]. The follow-up periods will be 12 and 24 months after treatment [31, 35] (Fig. 1).

#### Radiographic procedures

The child safety will be properly managed by the use of lead apron thyroid collar and ultraspeed x-ray films. The focus/film distance will be approximately 20 cm, assured by universal acrylic positioning stents. A dental x-ray device with 70 kV and 10 Ma will be used. The exposure time will be 0.5 s. All radiographs will be standardized using universal acrylic positioning stents (Han-Shin type). The periapical radiographs will be taken at preoperative, immediate postoperative, and 12 and 24 months of follow-up [30] (Fig. 1).

### Sample size

The minimum sample size calculation was performed based on data from a previous study that found clinical and radiographic success of 94.73% for teeth treated with MTA [14]. For the sample calculation, alpha and beta errors of 5% and 20% will be respectively considered. The sample size also provides 80% power. The sample will be of 143 teeth per group to detect significant differences. A dropout rate of 20% will be estimated, and then, the number of eligible teeth will be 234 per group.

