**Methods:**

Four hundred and sixty-eight teeth from children aged between 5 and 9 years old, both genders, with deep caries lesion with pulp involvement, but no furcal impairment and any sign of necrosis will be selected. The vital pulp therapy will be performed with mineral trioxide aggregate (control group) and dentin-pulp biostimulation chitosan membrane (BBio group). The clinical and radiographic outcomes will be assessed at 12 and 24 months after treatment. The thickness of the dentin barrier will be verified through *Image J2* software. The Wilcoxon signed rank test and Mann-Whitney test will respectively compare the intra- and intergroup clinical and radiographic outcomes. Paired *t* test and independent *t* test will respectively compare the intra- and intergroup radiographic measurements. The logistic regression will be applied, and the degrees of this association will be measured using odds ratio (OR) and 95% confidence interval (95% CI).

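### The enrolment target of 234 teeth per group does not follow from 143 per group and 20% dropout, which give 179

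*Protocol article*

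**What the plan says.** The Sample size section of the protocol article starts from a previous study that "found clinical and radiographic success of 94.73% for teeth treated with MTA". It sets the error rates ("alpha and beta errors of 5% and 20% will be respectively considered") and adds: "The sample size also provides 80% power". The resulting requirement is: "The sample will be of 143 teeth per group to detect significant differences". The last step is the dropout allowance: "A dropout rate of 20% will be estimated, and then, the number of eligible teeth will be 234 per group".

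The Methods part of the Abstract gives the matching total, "Four hundred and sixty-eight teeth from children aged between 5 and 9 years old", and 468 = 2 × 234. Under Study design the unit is one tooth per child ("One primary tooth per patient will be randomly allocated in each group"), so numbers of teeth are numbers of children. Under Clinical procedures, "The follow-up periods will be 12 and 24 months after treatment".

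The section gives no success rate for the BBio group, no difference or margin to be detected, and no sidedness for the test.

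**The concern.** The wording presents 234 as the result of applying a 20% dropout allowance to 143. An uplift from 143 to 234 is far larger than 20% dropout calls for. Because the Abstract repeats the doubled figure, 234 is the number the trial works to and not an isolated misprint.

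At stake is the justification for the number of children enrolled. Each tooth is a child who has a pulp procedure and a series of radiographs, and half are to receive a new material. A target well above what the stated inputs require needs either correcting or explaining. As the text stands, a reader also cannot tell how many evaluable teeth the trial expects at the end of follow-up: 143, or the 187 that 234 with 20% loss would leave.

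**Working it through.** **Inputs, all from the Sample size section:** 143 per group before dropout; dropout d = 20%; target 234 per group; MTA success 94.73%; alpha 5%; power 80%. From the Abstract: 468 in total.

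**Step 1: try to reproduce 234 from 143 and 20%.**
- Standard inflation, n/(1 − d): 143/0.8 = 178.75, so 179 per group, 358 in total.
- Common shortcut, n × (1 + d): 143 × 1.2 = 171.6, so 172 per group, 344 in total.
- 20% lost at each of the two follow-up visits: 143/0.8² = 143/0.64 = 223.4, so 224 per group.
- The shortcut applied twice: 143 × 1.2² = 205.9, so 206 per group.

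None of these gives 234.

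**Step 2: size of the gap.** 234 − 179 = 55 per group; 468 − 358 = 110 in total; 234/179 = 1.31, so the target is about 31% above the standard result.

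**Step 3: what 234 leaves.** 234 × 0.8 = 187.2, so 187 evaluable per group, which is 44 more than 143.

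**Step 4: where 143 comes from.** The documents do not give enough to derive it. As an assumption, take BBio success of 84.73% (10 points below MTA), a two-sided 5% test, 80% power and the pooled-variance formula without continuity correction:

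n = [1.960 × √(2 × 0.8973 × 0.1027) + 0.842 × √(0.9473 × 0.0527 + 0.8473 × 0.1527)]² / 0.10²
= [1.960 × 0.4293 + 0.842 × 0.4234]² / 0.01 = 143.5.

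This is close to 143, although the usual rounding up would give 144. Other assumptions also lead to 143. The BBio rate for which 143 per group gives 80% power is:
- about 83.8%, two-sided with continuity correction;
- about 84.7%, two-sided without it;
- about 85.2%, one-sided with it;
- about 86.1%, one-sided without it.

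**Step 5: power, on the assumption of 94.73% against 84.73%, two-sided 5%.**

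| Evaluable per group | Power |
|---|---|
| 143 | about 80% |
| 179 | about 88% |
| 187 | about 89% |

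**The case against.** The strongest reply is that nothing is put at risk. The section calls its calculation a minimum, and 187 evaluable teeth per group exceeds it, so power is at least what was claimed and neither the estimate nor the test is biased. This stands. A reader might infer that sample size, dropout and power cannot all be true together. The documents do not support that: 80% power as a minimum is compatible with enrolling 234 and losing 20%. Only the step from 143 to 234 fails.

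A second reply is that the target counts eligible teeth, and the Eligibility section excludes teeth during the procedure when hemostasis is not reached. Some of the excess might cover such losses. That makes the count of additional children treated less certain, but it does not rescue the arithmetic. Dropout is the only adjustment named, no rate for other losses is given, and a figure per group points to allocated teeth.

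Two further inferences are tempting and should not be drawn:
- Since 1 − 143/234 = 38.9%, a reader might conclude that the real planned loss is about 39% and that attrition bias has been understated. The plan states 20%, and the Discussion openly lists high dropout as a limitation. The 38.9% is only a back-calculation from figures that do not fit.
- Since 234/1.2 = 195 exactly, a reader might suppose that the true base was 195. No part of the document mentions that number.

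Finally, any power figure above 80% depends on an effect the plan never states. The null hypothesis in the Background is worded as comparable success, so even a two-sided comparison for difference is an assumption.

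**Conclusion.** The point holds as an arithmetic inconsistency in the enrolment target. Applied to 143 per group, 20% dropout gives 179 (358 in total), or at most a case for 172 (344 in total) by the shortcut; it does not give 234 (468 in total). The excess is 55 per group, 110 in total, over the standard result, with no explanation in the text. This conclusion needs no assumption beyond the figures in the Sample size section.

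The error does not threaten the stated 80% power. The documents do not show which of the three figures is wrong, or whether an inflation step was left out. The power of about 89% at 187 per group holds only if the design difference was 94.73% against 84.73% with a two-sided 5% test.

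**What to change.** Rewrite the Sample size paragraph so that each number follows from the one before, and make the Abstract total agree. Two coherent versions are open to the sponsor:

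1. State 143/0.8 = 179 per group, 358 in total.
2. Keep 234 per group, 468 in total, and state that 20% loss leaves 187 evaluable per group, why the target is larger than 143 requires, and what power it gives.

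In either version, state the BBio success rate or difference, and the sidedness, that produced 143, so that the figure can be checked. If these were 84.73% and two-sided 5%, the power to report at 187 is about 89%.

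The cost is a few sentences in the Sample size section and, for the first version, one number in the Abstract. No additional children are needed. Trial status plans recruitment to end in September 2020, before the article's October 2020 publication date, so cutting enrolment may no longer be possible. In that case the second version is the practical one.
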